### b) Hypothesised Mechanisms of Change (RQ3)

*Drinking motives* across four dimensions (social, conformity, enhancement, and coping motives) will be assessed by the Drinking Motives Questionnaire-Revised (Grant et al., 2009). High risk personality traits will be assessed using the *Substance Use Risk Profile Scale (SURPS)* personality questionnaire (Woicik et al., 2009). *History of trauma* will be examined using the Life Events Checklist (Weathers et al., 2013a). *Perceived peer use of alcohol and cannabis* will be measured using 5 items ([name] et al., 2010) that gauge participants' estimation of the proportion of their friends who consume alcohol and cannabis. *Self-efficacy to resist peer influences* will be assessed using an adapted 8-item version of Bandura's Resistive Self-Regulatory Efficacy Scale ([name] et al., 2014; Bandura et al., 2003). *Emotional and behavioural problems* will be assessed using the Kessler-6. Specific depression and anxiety symptoms will be measured by relevant subscales of the Brief Symptom Inventory (Derogatis et al., 1993). Capacity to modulate emotional reactions and associated behaviours will be assessed with the Emotion Regulation Questionnaire (Gross et al., 2003). Sleep, diet and sedentary behaviour will be measured using items from the International Physical Activity Questionnaires as adapted by Ding et al. (2015).

## 4. Sample Size (Maximum of 250 Words)

Outline the intended sample size for the project and justify how this will meet the aims of the study.

Sample size calculations tools can be found online at:

- <http://powerandsamplesize.com/Calculators/> (quantitative)
- <http://stat.ubc.ca/~rollin/stats/ssize/index.html> (quantitative)
- [http://eprints.ncrm.ac.uk/2273/4/how\\_many\\_interviews.pdf](http://eprints.ncrm.ac.uk/2273/4/how_many_interviews.pdf) (qualitative)

Participants for this study are 2,190 individuals who were recruited to the original CAP study as students in 2012. Power calculations for the original trial were based on recent methods developed to account for cluster randomisation (Heo et al., 2009). These calculations assumed 20% drop-out, and indicated a total of 1,920 participants recruited from 24 schools would achieve 80% power to detect a between-group mean difference of 0.15 ( $p < 0.05$ ). For comparisons among high risk participants, 600 students from 20 schools would achieve 80% power to detect a standardized between-group mean difference of 0.3. In our original study we achieved well over this recruitment target, with 2,190 students and 947 high-risk students participating in the study.

## 5. Research Participants (Maximum of 500 words)

Describe the characteristics of the participants that you intend to recruit in the study (e.g. inclusion/exclusion criteria, sex, age range of participants).

Participants for this study are 2,190 young people (57% male) from 26 Sydney schools recruited to the original CAP study in 2012 who have provided their non-school locator information online. At the 5 year follow up in 2017 almost all participants will be between 18 and 19 years of age. Study participants who have actively withdrawn consent to participate will not be contacted. All remaining subjects will be contacted to and invited to consent to participate in Survey 5, 6 and 7.

## 6. Recruitment of participants

Outline the methods that will be used to recruit participants to the study. The methods in this section should describe:

- What process(es) will be used to identify potential participants;
- How initial contact will be made with potential participants;
- How participants will be screened to ensure they meet the inclusion criteria.

Participants will be located using multiple sources of locator information already provided by the subject. This includes email, phone number, postal address, Facebook handle, and parents' email address. Participants will be invited to complete online assessments at the 5 (2017), 6 (2018) and 7 (2019) year time points. Participants will be contacted in 2017 and invited to participate in the extended follow-up study. Only participants who consent will be subsequently contacted by project staff. Study participants who have actively withdrawn consent to participate will not be contacted.

## 7. Consent

Provide a detailed description of the consent process to include the following:

- The type of consent that will be sought (e.g. verbal/ written/ return of survey etc.), how and when you will provide consent materials to your potential participants and why this method of consent is appropriate for the participant population.
- How, when and to whom participants will indicate their consent and how any real or perceived coercion will be avoided during the consent process.

**\*\*if the project involves the use of data already collected and the participants have already provided their consent for this to happen, please attach a copy of the original consent form as evidence.**

**\*\*if you are seeking a waiver of consent, please provide justification. (See the National Statement, Chapters 2.2 and 2.3 for more information).**

In line with follow-up procedures used in waves 1-4, participants will be contacted via email or phone in 2017 and will be invited to consent to completing three additional surveys. Participants will also be asked for consent for their name and date of birth to be released to the Reoffending Database at the Bureau of Crime Statistics and Research (BOCSAR), and to the National Death Index (NDI) Database at the Australian Institute of Health and Welfare (AIHW).

Linking to the Reoffending Database at BOCSAR will allow for an objective measure of drug and alcohol related problems and self-reported aggression and criminal involvement. This is particularly important given the strong association between drug use and crime where two in every three offenders (66%) who are detained by police are under the influence of at least one drug – not including alcohol (Payne & Gaffney, 2012). Participants will be advised that, should consent be given for data linkage, the information collected will be offence type, date of offence and penalty. Participants will be asked to consent to data linkage occurring on three occasions (2017, 2018 & 2019). Participants will be informed that this information will be collected to better understand the relationship between drug use and crime with the aim of informing prevention initiatives.

Linking of participant data to the NDI at the AIHW will allow for a deeper understanding of the relationship between substance use, mental health, psychological and environmental factors. Participants will be informed of the exact information that will be obtained from the NDI. Participants will be advised that, should consent be given, the information that will be requested will be all information stored in the NDI database, fact of death information (e.g. date of death, state/territory the death was registered in, year the death was registered) and cause of death information (e.g. underlying and other causes of death). Participants will also be asked for consent to repeat data linkage with NDI i.e. for each of the three follow-up survey occasions in 2017, 2018 and 2019. Participants will be informed that this data will be utilised to analyse survival rates and mortality outcomes of CAP study participants, and also to ensure that no deceased persons are contacted to participate in follow-up surveys.

It will be stressed to participants that they are not required to consent to the data linkage, and can withdraw consent from data linkage or other aspects of the study at any time. The participant information sheets state clearly that involvement in the study is voluntary and that a decision whether or not to participate will not prejudice future relations with The University of New South Wales or the researchers (see attachment). It also states that participants are free to

withdraw at any time without giving a reason and without penalty.

## 8. Reimbursement of Expenses or Incentives to Participate

Explain whether there will be any reimbursement of out-of-pocket expenses, financial incentive or other “reward” as a result of participation in the study.

All participants will go into the draw to win an iPad (valued at \$400) or a \$400 JB HIFI voucher at the end of each survey occasion. In addition, those who complete all surveys (5, 6 & 7) will go in a draw to win an iPad at the end of the follow-up period (one per 2 schools). Participants will not be reimbursed for consenting to the data linkage component of the study.

## 9. Risks to participants

Describe the anticipated risks to the participants, including:

- Whether the benefits outweigh the risks to the participants;
- How will you manage or minimise the risks to participants.

There are no major foreseeable risks involved with participation in this study. Although unlikely, it is possible that some individuals may experience emotional discomfort as the questionnaire asks about use of alcohol and other drugs and mental health symptoms. It is also possible that participants may feel some mild distress as this questionnaire may ask you to disclose information about engaging in illegal activity (i.e. consuming illicit drugs). Participants will be made aware that they have the right to stop completing the questionnaire at any time, and that they can withdraw from the study. Participants will also be provided with contact details of the study co-ordinators, for support services (e.g. Lifeline) and the Alcohol and Drug Information Service at the end of the survey.

BOSCAR Reoffending Database (ROD) linkage – Potential Risks: There are no major risks associated with providing consent to record linkage with the ROD as confidentiality of this information will be strictly maintained by BOSCAR and the study investigators. Only de-identified information will be used for the purposes of analysis and any research findings will be published in a way that ensures that participating individuals cannot be identified.

AIHW National Death Index (NDI) database linkage – Potential Risks: There are no major risks associated with providing consent to record linkage with the NDI. All information will remain strictly confidential and will be maintained by the Registrars of Births, Deaths and Marriages, AIHW and the study investigators. Only de-identified information will be used for the purposes of analysis and any research findings will be published in a way that ensures that participating individuals cannot be identified.

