## Schedule of Assessments

Table 1 shows assessments completed as part of the original CAP trial, and proposed extended follow-up assessments. Using multiple sources of locator information already provided to the research team, all participants will be invited to complete online assessments at 5-, 6- and 7- years. Participants will complete surveys online via the CAP study website ([www.capstudy.org.au](http://www.capstudy.org.au)). Participant responses will be linked over time using a unique identification code to ensure confidentiality.

Table 1: Completed CAP study assessments and timeline for extended follow-up assessments

| Original CAP trial                                                                                                                         |                                             |                                             |                                             | Timeline for Extended Follow-up |                   |                |
|--------------------------------------------------------------------------------------------------------------------------------------------|---------------------------------------------|---------------------------------------------|---------------------------------------------|---------------------------------|-------------------|----------------|
| 2012                                                                                                                                       | 2013                                        | 2014                                        | 2015                                        | 2017                            | 2018              | 2019           |
| Year 8                                                                                                                                     | Year 9                                      | Year 10                                     | Year 11                                     | Post-school +1                  | Post-school +2    | Post-school +3 |
| Baseline + Intervention
n = 2,190                                                                                                | 1-year F/U survey
n = 1,818 (83%) | 2-year F/U survey
n = 1,732 (79%) | 3-year F/U survey
n = 1,601 (71%) | 5-year F/U survey               | 6-year F/U survey | 7-year F/U     |

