## 10. Privacy and Confidentiality

Outline the methods that will be applied to ensure that the privacy of participants is protected during:

- The recording and analyses of data;
- The storage of data;
- Publishing or reporting the information.

Confidentiality of collected information will be strictly maintained and all data collected will be done anonymously so there will be no identifying information on any data collected. The survey information collected from the participants will be allocated a username (for online surveys). Participants who do not have access to the internet and require a paper and pencil survey will be given a special code. This is for the purposes of linking the survey data collected at each follow up stage. At no stage will the participants’ names be connected with their data i.e. not on the original data collected or in the saved data files.

Online data: To access the online surveys, participants will be required to logon to the CAP study website using their unique username (email address) and password. Once logged in, all data collected will automatically be de-identified and the database will generate a unique code for each participant. The individual’s data files across sessions will be linked with this unique code.

SSL (Secure Sockets Layer) Security will be used to ensure any confidential communication via the website (e.g. participant registration and online surveys) is kept secure. SSL provides a mechanism to verify the identity of an internet client and/or server, and to encrypt the messages sent between them. All data will be stored on secure serves hosted in Australia.

Paper data: Some participants may wish to complete surveys with pen and paper rather than online. In this case, participants use a unique code (made up of easily remembered fragments of personal information) each time they fill in a survey and this code will be used to link their surveys over time. Only the researcher will have access to these codes.

No information will be published on individual cases, with all published data being group data.

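### Online extension surveys: the one stated place for the support contacts is the end of the survey, which a participant who stops part-way does not reach

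*Protocol*

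**What the plan says.** Section 9 of the Project Description (Risks to participants) accepts that questions on substance use, mental health symptoms and illegal activity may upset some respondents, although it considers this unlikely. It then lists its safeguards. The first is a right to break off: "Participants will be made aware that they have the right to stop completing the questionnaire at any time". Withdrawal from the study is also open to them. The next sentence deals with support: "Participants will also be provided with contact details of the study co-ordinators", and the list goes on to support services, with Lifeline as the example, and "the Alcohol and Drug Information Service at the end of the survey".

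The surveys are web-based. Under Schedule of Assessments, "Participants will complete surveys online via the CAP study website", at 5, 6 and 7 years. Section 10 (Privacy and Confidentiality) adds that "participants will be required to logon to the CAP study website using their unique username" and a password, and allows paper for some participants.

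On contact with participants, section 6 (Recruitment of participants) says: "Participants will be contacted in 2017 and invited to participate in the extended follow-up study". Section 7 (Consent) says that "participants will be contacted via email or phone in 2017 and will be invited to consent to completing three additional surveys". Section 7 also refers to participant information sheets as an attachment, which is not among the material shown.

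**The concern.** The two safeguards stand in consecutive sentences but do not work together. A participant who uses the first (stopping) leaves before the one stated delivery point of the second (the contacts). Someone who stops because an item was distressing is among those most likely to need the contacts, so the stated rule misses part of the group it is meant for.

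The survey content makes this more than a formality. Under Measures, the extension asks about trauma history (Life Events Checklist), self-reported violence, psychiatric symptoms (a DSM-5 symptom checklist), and depression and anxiety symptoms. No facilitator is described for the online surveys.

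What is at stake is participant care alone. The point does not bear on any outcome, estimate or analysis.

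**Working it through.** The plan gives no figure to reproduce on this point, and no alpha, power or sample-size quantity enters. The check is a reading of the relevant sections side by side, with simple counts.

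**Step 1: where the contacts are delivered.** Section 9 states one point, the end of the survey. The timing phrase could be read as governing only the last item in the list (the Alcohol and Drug Information Service). On that reading the co-ordinator and support-service contacts have no stated delivery point at all, which does not help someone who stops early.

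**Step 2: who reaches that point.** A participant who completes the survey reaches 1 of 1 stated points. An online participant who stops part-way reaches 0 of 1.

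**Step 3: whether another section fills the gap.** The rest of the Project Description was read for a second delivery point:

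- Schedule of Assessments gives the mode (study website) and does not mention the contacts.
- Section 10 describes the logon step and does not place the contacts there.
- Sections 6 and 7 describe invitation and consent and do not mention support contacts.

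None puts the contacts on the opening page, on each page or on early exit.

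**Step 4: comparison with the original school trial.** In the Protocol's summary of known and potential risks and benefits, a facilitator explains the support options at the start of every baseline and follow-up session, and the same text is printed at the end of each questionnaire. That is 2 delivery points, and a student who stopped part-way had already met the first. The online extension keeps the closing one and describes no equivalent of the opening one. The school procedure does not contradict section 9, because it covers facilitator-led sessions. It does show that the investigators previously used delivery at both start and end.

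**Step 5: how many surveys are involved.** Three online surveys: 2017, 2018 and 2019.

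**Step 6: the consent contact as a possible substitute.** The one consent contact described is in 2017 and covers all three surveys. The intervals from that contact are:

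- 2017 survey: 2017 − 2017 = 0 years
- 2018 survey: 2018 − 2017 = 1 year
- 2019 survey: 2019 − 2017 = 2 years

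If the information sheet lists support contacts, it would therefore have been given about one and two years before the later surveys. This is a side argument and carries little weight: it adds nothing for the 2017 survey, and section 6 describes further contact at later waves.

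**Step 7: number of participants affected.** The Protocol gives no rate of stopping because of distress, so none is calculated.

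**The case against.** The strongest reply is that this is page-layout detail rather than an error. Section 9 states nothing false, calls the risk unlikely, and does not say that the contacts appear only at the end. Four further points support that reply.

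- **Unseen material.** The information sheets are the natural place for support contacts, and their absence from the reviewed text is not an omission in the plan. This stands: contacts may well have been supplied before a survey. It does not show that they are delivered when someone stops.
- **Later invitations.** Section 6 describes inviting participants to the 2018 and 2019 surveys as well, and anyone who completed the 2017 survey would already have been given the contacts. This also stands, and it is why the one- and two-year intervals should not be pressed. What the later invitations contain is not described.
- **Software behaviour.** The survey system might send early leavers to the closing page. The Protocol does not say so, and closing the browser would bypass it.
- **Prior exposure.** Almost all participants will be 18 or 19 in 2017, and the cohort's school surveys were planned with support options given at start and end. An early stopper is thus less likely to be unaware of any help. That lowers the stakes without closing the gap.

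Together these objections show that contacts could reach a participant by another route. None shows that the plan provides them at the point of stopping. Because the document names a specific delivery point, and that point misses early leavers, this is a stated rule that falls short rather than a detail merely left open.

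**Conclusion.** The point holds, as a minor one. For the three online extension surveys, the single stated delivery point for the support contacts is one that a participant who stops part-way does not reach.

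The conclusion rests on the Project Description as shown and is limited to what that text assures at the moment of stopping. It assumes no unstated routing of early leavers and makes no claim about the content of the unseen information sheets or later invitations. It does not extend to paper completion. No contradiction between sections, no number of affected participants and no effect on the trial's results is claimed.

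**What to change.** In section 9 of the Project Description, add one sentence saying that the same contacts will also be shown on the opening page of each online survey (for example, directly after the logon that section 10 already requires) and on an early-exit page, as well as at the end. Showing them on every page would serve equally well, and would also cover someone who simply closes the browser.

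The cost is that sentence and a small change to the survey web pages, reusing contacts already prepared. No new content, staff or visits are needed, and measures and analyses are unchanged.

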## 10. Privacy and Confidentiality

Outline the methods that will be applied to ensure that the privacy of participants is protected during:

- The recording and analyses of data;
- The storage of data;
- Publishing or reporting the information.

Confidentiality of collected information will be strictly maintained and all data collected will be done anonymously so there will be no identifying information on any data collected. The survey information collected from the participants will be allocated a username (for online surveys). Participants who do not have access to the internet and require a paper and pencil survey will be given a special code. This is for the purposes of linking the survey data collected at each follow up stage. At no stage will the participants’ names be connected with their data i.e. not on the original data collected or in the saved data files.

Online data: To access the online surveys, participants will be required to logon to the CAP study website using their unique username (email address) and password. Once logged in, all data collected will automatically be de-identified and the database will generate a unique code for each participant. The individual’s data files across sessions will be linked with this unique code.

SSL (Secure Sockets Layer) Security will be used to ensure any confidential communication via the website (e.g. participant registration and online surveys) is kept secure. SSL provides a mechanism to verify the identity of an internet client and/or server, and to encrypt the messages sent between them. All data will be stored on secure serves hosted in Australia.

Paper data: Some participants may wish to complete surveys with pen and paper rather than online. In this case, participants use a unique code (made up of easily remembered fragments of personal information) each time they fill in a survey and this code will be used to link their surveys over time. Only the researcher will have access to these codes.

No information will be published on individual cases, with all published data being group data.

**BOCSAR Reoffending Data:** In order for data linkage to occur, identifiable information would need to be released to BOCSAR (so long as participant consent is provided for this data to be shared). Confidentiality of this data would be strictly maintained by BOCSAR. BOCSAR has minimized the risk to personal privacy by ensuring that the data will be stored on a password protected computer network in a secure location. BOCSAR has a Code of Practice under Part 3 Division 1 of the Privacy and Personal Information Protection Act 1998. The Code of Practice was developed in consultation with the Privacy Commissioner and made by order of the Attorney General. This code of practice has provisions to ensure that BOCSAR does not disclose personal information provided by agencies.

**AIHW National Death Index database:** Identifiable information would be required to be released to the AIHW in order for record linkage to occur. There is an agreement between the AIHW and the Registrars of Births, Deaths and Marriages, which covers the restrictions on the use and release of the information provided. Under this agreement, the Registrars are regularly notified of all NDI linkage projects. A Registrar is a member of the AIHW Ethics Committee, and the confidentiality conditions of the AIHW Act 1987 apply to data provided by NDI users.

